## Abstract

**Background:**

Respiratory support following postoperative extubation is of major importance to prevent hypoxemia and subsequent respiratory failure and reintubation. High-flow nasal cannula oxygen (HFNC) delivers a flow-dependent positive airway pressure and improves oxygenation by increasing end-expiratory lung volume. Whether application of HFNC may have therapeutic advantages over conventional oxygen therapy for respiratory support in the early postextubation surgical period remains to be established.

**Methods/design:**

The Optiflow for prevention of post-extubation hypoxemia after abdominal surgery (OPERA) trial is an investigator-initiated multicenter randomized controlled two-arm trial with assessor-blinded outcome assessment, randomizing 220 patients with intermediate to high risk of pulmonary complications after abdominal surgery to receive HFNC or conventional oxygen therapy following extubation, stratified by the presence of epidural analgesia and center. The primary outcome measure is the percentage of patients with postoperative hypoxemia one hour after tracheal extubation. Secondary outcome measures are postoperative pulmonary complications, need for noninvasive ventilation and intubation for respiratory failure.

**Discussion:**

The OPERA trial is the first randomized controlled study powered to investigate whether early application of HFNC following extubation after abdominal surgery prevents against postoperative hypoxemia and pulmonary complications.

**Trial registration:**

ClinicalTrials.gov Identifier: NCT01887015.

## Background

Recent data suggest that more than 200 million major surgical procedures are performed worldwide each year [1]. Postoperative respiratory complications still remain a frequent problem, thereby increasing postoperative morbidity and mortality, [2] and putting a burden on hospital length of stay and costs of health care [3].

Respiratory support is of major importance following extubation to avoid respiratory failure and reintubation. It has been reported that postoperative hypoxemia complicates between 30% and 50% of cases after abdominal surgery, even among those undergoing uneventful procedures [4,5]. After extubation and with spontaneous breathing at ambient air, derecruitment of lung areas and loss of functional alveolar units may rapidly occur leading to hypoxemia [6]. Supplemental oxygen administration, usually by the use of nasal prongs or a facemask, is required to ensure adequate arterial oxygenation after extubation [7]. However, although oxygen therapy is effective in treating most cases of postoperative hypoxemia [8], low ventilation-perfusion ratios may be only partially responsive to an increase in oxygen concentration [9]. In addition, oxygen therapy is only a symptomatic approach and is ineffective to compensate for loss in lung volume. In contrast, the noninvasive application of continuous positive airway pressure is effective to maintain lung volume and to improve gas exchange after major surgery [10]. A randomized controlled study authored by Squadrone and colleagues [11] demonstrated that application of continuous positive airway pressure (CPAP) may reduce the need for reintubation, pneumonia and postoperative sepsis in patients who developed acute hypoxemia (defined as an arterial oxygen tension to inspiratory oxygen fraction ratio (PaO_2_/FiO_2_) of 300 mmHg or less) after elective major abdominal surgery. However, patient cooperation and tolerance, air leaks and gastric distension are crucial for application and success of CPAP or noninvasive ventilation (NIV). Moreover, NIV affects health-care utilization, since its application usually requires admission to intensive care or within care structures capable of providing high levels of monitoring.

High-flow nasal cannula (HFNC), which delivers high-flow heated and humidified oxygen and air via nasal prongs at a prescribed fraction of inspired oxygen and a maximum flow of 60 L/min, is an attractive alternative to conventional oxygen therapy [12,13]. Previous studies have shown that HNFC oxygen therapy generates a flow-dependent positive airway pressure [13,14] and improves oxygenation by increasing end-expiratory lung volume, thus suggesting a possible alveolar recruitment associated with high-flow therapy [15]. Although prophylactic use of HFNC may have potential therapeutic advantages over conventional oxygen therapy for respiratory support after extubation, evaluation is limited in the early post-extubation surgical period and benefit remains to be established.

The OPERA study aims to compare the effects of early application of HFNC oxygen therapy and conventional oxygen administration after extubation on postoperative pulmonary complications in patients with intermediate to high risk of postoperative pulmonary complications after abdominal surgery.

## Methods/design

### Objectives and design

The Optiflow for prevention of post-extubation hypoxemia after abdominal surgery (OPERA) study is an investigator-initiated multicenter randomized controlled two-arm trial. The Institutional Review Board of the University Hospital of Clermont-Ferrand (France) approved the trial. By April 25 2013, the study had been approved by all centers by a central ethics committee (Comité de Protection des Personnes Sud-Est VI, Clermont-Ferrand, France) with the registration number IDRCB 2013-A00030-45. The OPERA study is conducted in accordance with the declaration of Helsinki and was registered on June 24 2013 at http://www.clinicaltrials.gov with trial identification number NCT01887015.

### CONSORT diagram

Figure 1 shows the CONSORT diagram of the OPERA trial.

**Figure 1 F1:**
[figure not shown]
CONSORT diagram of the OPERA trial.

### Study population

Local investigators screen consecutive patients scheduled for planned or unplanned abdominal or abdominal and thoracic surgery with an expected duration of two hours or more in participating centers. Patients with intermediate to high risk for postoperative pulmonary complications following abdominal surgery with general anesthesia are eligible for participation. To identify such patients, the ARISCAT risk score will be used [16]. An ARISCAT risk score ≥26 is associated with an intermediate to high risk for postoperative pulmonary complications.

Patients fulfilling one or more of the following criteria will not be included: lack of informed consent prior to randomization (for an unplanned surgical procedure consent is obtained from the next of kin), nonadult patients (age <18 years), patients with a body mass index ≥35 kg/m^2^, a life-threatening condition requiring emergency surgery, patients with obstructive sleep apnea, and pregnant patients to provide a relatively homogenous study population and avoid potential confounding in the interpretation.

All patients are asked for signed informed consent, as required by the institutional review board in accordance with the Declaration of Helsinki.

### Randomization

Randomization is performed using a dedicated centralized telephone system, accessible round the clock, and using a computer-generated allocation sequence. The randomization sequence is generated using random blocks and is stratified per center and according to the planned use or nonuse of postoperative epidural analgesia, which is a factor that may influence outcomes [17]. No blocking is applied to other trial factors.

### Trial interventions

Patients eligible for inclusion following extubation after abdominal surgery are randomly assigned to standard oxygen therapy via either nasal prongs or face mask with oxygen flow titrated by the bedside clinician to maintain a peripheral oxygen saturation of 95% or more, or HFNC oxygen therapy at a flow rate of 50 to 60 L/min and FiO_2_ titrated by the bedside clinician to maintain a peripheral oxygen saturation of 95% or more. In each group, extubation criteria after surgery are: recovery of spontaneous ventilation with an expired tidal volume between 5 and 8 ml/kg, respiratory rate between 12 and 25 breaths/min, absence of residual neuromuscular blockade (assessed by a T4/T1 ratio ≥90%), peripheral oxygen saturation ≥95%, stable hemodynamics and a body temperature ≥36°C. HFNC oxygen therapy is delivered via the Optiflow™ system (Fisher & Paykel Healthcare Ltd, Auckland, New Zealand) using a MR850 heated humidifier and a RT202 breathing circuit. Allocated therapy is delivered until 0700 to 0800 hours postoperative day 1 at which time point study therapy is discontinued and requirement for supplemental oxygen therapy is assessed.

### Standard procedures

The recently completed Intraoperative Protective Ventilation (IMPROVE) trial showed significantly improved clinical outcomes (10.5% versus 27.5%, *P* <0.001) in patients who received intraoperative lung-protective mechanical ventilation compared with those receiving NIV [18]. Therefore, the study protocol stresses that intraoperative lung-protective mechanical ventilation must be used in the OPERA trial.

All other aspects of patient care during the intra- and postoperative periods, including general anesthesia, fluid administration, prophylactic antibiotics and postoperative pain management, are conducted by the attending physician according to the expertise of the staff at each center and routine clinical practice. However, it is suggested to perform postoperative pain management to achieve a visual numerical scale (VNS) pain score <3, to avoid excessive administration of intraoperative fluids (according to the discretion of the attending anesthesiologist), and to use appropriate prophylactic antibiotics. Data on the applied procedures will be collected and analyzed.

### Study endpoints

Primary outcome variable is the percentage of patients who developed postoperative hypoxemia one hour after tracheal extubation. Postoperative hypoxemia is defined as PaO_2_/FiO_2_ ratio <300, as used previously [11].

Secondary outcome variables are postoperative gas exchange one hour after extubation and after discontinuation of the allocated treatment, respiratory discomfort (using a numerical rating scale, ranging from 0 to 10), need for supplemental oxygen therapy (defined as arterial oxygen saturation <93% on room air), need for postoperative reintubation and/or NIV for acute respiratory failure within the first seven days after surgery, postoperative pulmonary complications within the first seven days after surgery, unexpected intensive care unit (ICU) admission or readmission, ICU and hospital length of stays, and in-hospital mortality. Acute respiratory failure is defined by one of the hypoxemic criteria (peripheral oxygen saturation (SpO_2_) <92% while breathing at least 10 L/min oxygen, PaO_2_ <60 mmHg on air or PaO_2_ <80 mmHg while breathing any supplemental oxygen) and at least one of the following criteria: severe respiratory distress with dyspnea, accessory muscle recruitment and paradoxical abdominal or thoracic motion, respiratory rate >25 breaths/min, respiratory acidosis with pH <7.30 and arterial carbon dioxide partial pressure (PaCO_2_) >50 mmHg [19]. Postoperative pulmonary complications are scored with the use of a graded scale [20] from 0 (no pulmonary complications) to 4 (the most severe complications). Postoperative pulmonary complications are defined as: atelectasis (opacification of the lung with shift of the mediastinum, hilum or hemidiaphragm toward the affected area and compensatory overinflation in the adjacent nonatelectatic lung); suspected pulmonary infection (patient receives antibiotics and meets at least one of the following criteria: new or changed sputum, new or changed lung opacities on chest X-ray when clinically indicated, tympanic temperature >38.3°C, white blood cell (WBC) count >12,000/μl in the absence of other infectious focus); pleural effusion (chest X-ray demonstrating blunting of the costophrenic angle, loss of the sharp silhouette of the ipsilateral hemidiaphragm in upright position, evidence of displacement of adjacent anatomical structures or (in supine position) a hazy opacity in one hemithorax with preserved vascular shadows); and pneumothorax (air in the pleural space with no vascular bed surrounding the visceral pleura).

### Blinding

A computer program will generate the coding list and will allocate coding numbers to patients from the specific trial site. It is not feasible to mask the assigned oxygen therapy from the attending anesthesiologists, since they have an ethical responsibility to ensure patient safety until discharge from the post-anesthesia care unit. However, in each participating center, postoperative data will be collected and recorded onto case report forms (CRFs) by local research coordinators blinded to the randomized intervention. A trained research coordinator, blinded to the randomized intervention, will centralize data from all sites and will record them onto the electronic database.

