### Registration

Data will be collected and recorded onto CRFs in each center by trained local research coordinators blinded to the randomized intervention. A trained research coordinator will centralize data from all sites and will record them onto the electronic database.

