### The following data will be collected and registered

Prerandomization and baseline characteristics: gender, age, height, weight, ideal body weight, physical status (according to the American Society of Anesthesiology status score), cardiac status (hypertension, cardiac failure, ischemic heart disease), respiratory status (history of chronic obstructive pulmonary disease, asthma status, respiratory infection in the last month, long-term home oxygen therapy), smoking status, alcohol status, history of diabetes mellitus, recent denutrition (defined as weight loss >10% in the last six months and/or plasma albumin <30 g/l), history of renal insufficiency, ARISCAT score, preoperative SpO_2_, and blood samples (WBC count, hematocrit, hemoglobin, platelet count, prothrombin time, fibrinogen, urea, creatinine, C reactive protein and albumin).

During the surgical and anesthesia procedures: type of surgery (planned or unplanned), surgical site (abdominal or abdominal and thoracic), surgical technique (laparotomy or laparoscopy), duration of both anesthesia and surgical procedures, blood losses, transfusion requirement, all administered drugs during anesthesia (anesthetics, vasoactive drugs, neuromuscular blocking agent), all administered fluid (crystalloid, colloid), ventilator settings (tidal volume, positive end-expiratory pressure, recruitment maneuver, FiO_2_, plateau and peak pressures), duration of mechanical ventilation.

From randomization to postoperative day 1 (at which time point study therapy is discontinued): vital parameters, SpO_2_, visual analog scale (VAS) score for pain, VNS score for respiratory discomfort, arterial blood gases (PaO_2_, PaCO_2_, pH, bicarbonate test (HCO_3_), arterial oxygen saturation (SaO_2_)), all side effects related to the allocated oxygen therapy, presence or absence of postoperative pulmonary complications.

Daily from postoperative day 1 to day 7: vital parameters, need for supplemental oxygen administration, presence or absence of postoperative pulmonary complications (pulmonary complication, if present, is graded), chest-X ray when clinically indicated, need for intubation or noninvasive mechanical ventilation, need for ICU admission or readmission. The day of development of any pulmonary complication and/or ICU admission is indicated.

The day of hospital discharge: duration of ICU and hospital stays, survival status (the day of death, if present, is indicated).

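### The unqualified assessor-blinding claim does not fit the on-treatment data that the blinded coordinators must record, and it cannot be relied on for the one-hour primary outcome

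*Protocol article*

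**What the plan says.** The Methods/design paragraph of the abstract describes a "multicenter randomized controlled two-arm trial with assessor-blinded outcome assessment" and excepts no outcome.

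The Blinding section names one group that cannot be masked: "It is not feasible to mask the assigned oxygen therapy from the attending anesthesiologists". It then says that in each center "postoperative data will be collected and recorded onto case report forms (CRFs) by local research coordinators blinded to the randomized intervention". The Registration section repeats this for case report form (CRF) data in general: "Data will be collected and recorded onto CRFs in each center by trained local research coordinators blinded to the randomized intervention". Neither section names a second, unblinded recorder for the treatment period.

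The section listing the data to be collected gives, for randomization to postoperative day 1, items that include "VNS score for respiratory discomfort, arterial blood gases" and "all side effects related to the allocated oxygen therapy", as well as the presence or absence of pulmonary complications.

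Under Trial interventions, "Allocated therapy is delivered until 0700 to 0800 hours postoperative day 1". One arm has prongs or a mask with oxygen flow titrated; the other has high-flow nasal cannula (HFNC) at 50 to 60 L/min with FiO2 titrated. Under Study endpoints, the primary outcome is PaO2/FiO2 below 300 one hour after extubation.

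**The concern.** A person who does not know the allocation cannot record the side effects of the allocated therapy. Nor can that person readily collect bedside data from a patient who is wearing one of two plainly different devices. The claim and the data list conflict as written, and the primary outcome is measured during the period of conflict.

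Two things are at stake. Readers will take one-hour hypoxemia and the other early outcomes to have been assessed blind, when the text does not secure this. In addition, only one recording role is named. A coordinator who has learned the arm during treatment still knows it when classifying complications up to day 7, which is where blinding is feasible and useful.

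**Working it through.** The point rests on comparing statements within the article. Arithmetic serves only to confirm that no stated figure is affected and to show why the FiO2 entry is a sensitive item.

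**1. The plan's own figure.** Inputs from Statistics: 40% against 20% (a 50% relative reduction), two-sided alpha 0.05, power 90%. With pooled variance, mean rate 0.30 and no continuity correction:

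n per arm = [1.960·√(2·0.30·0.70) + 1.282·√(0.40·0.60 + 0.20·0.80)]² / 0.20² = (1.270 + 0.811)² / 0.04 ≈ 108.2, so 109.

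The article states 110 per arm, where power is 90.5%. The figure reproduces, and nothing in this point alters it.

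**2. The statements side by side.**

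| Item | When | Device on the patient? | Can a recorder be blind? |
|---|---|---|---|
| Side effects of the allocated therapy | Randomization to day 1 | Yes | No, the item itself refers to the allocation |
| Respiratory discomfort (patient-rated) | Randomization to day 1 | Yes | Not reliably; patients are not described as masked either |
| One-hour PaO2 | One hour | Yes | Yes, if read from the analyzer alone |
| FiO2 for the one-hour ratio | One hour | Yes | Not assured; it has to come from the device |
| Complications before removal | Randomization to day 1 | Yes | Not reliably |
| Gas exchange after discontinuation | After removal | No | Yes |
| Complications, day 1 to 7 | After removal | No | Yes, if the recorder has not already learned the arm |
| Length of stay, in-hospital mortality | After removal | No | Yes |

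The label and both statements about coordinators cover every row. The text supports them only for the rows after removal and for the PaO2 value.

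**3. Why the FiO2 entry matters.** The primary outcome is a ratio cut at 300. Taking an assumed PaO2 of 120 mmHg:

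- FiO2 0.36: 120/0.36 = 333
- FiO2 0.40: 120/0.40 = 300
- FiO2 0.44: 120/0.44 = 273

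A 10% difference in the FiO2 assigned thus moves a borderline patient across the cut.

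**4. What a shift would do if one occurred.** Assume no true effect (40% in both arms) and that recording lowered the HFNC rate by s points, with 110 per arm. With p̄ the mean of the two rates, SE = √(2·p̄·(1−p̄)/110), and the two-sided rejection rate is 1 − Φ(1.96 − s/SE) + Φ(−1.96 − s/SE). For s = 0.05: p̄ = 0.375, SE = 0.0653, s/SE = 0.766, rejection about 12%. For s = 0.02 it is about 6%, and for s = 0.10 about 34%, against the nominal 5%. These values of s are assumed; the document gives no basis for choosing among them.

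**The case against.** The strongest reply is that this is a matter of wording. Collecting and recording onto a CRF is compatible with abstraction from charts, and an article commonly leaves to the full protocol who draws the gases and how coordinators are shielded. That holds for the missing operational detail. It does not resolve the conflict, because a chart entry on side effects of the allocated therapy also discloses the allocation, and the blinding statements are explicit and unqualified.

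Other objections stand and limit the point:

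- **FiO2 on the coordinator's form.** A reader might infer that the coordinators enter device settings and an FiO2 that gives the arm away. The article does not say so. Its list after randomization has no FiO2, flow or device field; FiO2 appears only among the intraoperative ventilator settings. The endpoint definition requires an FiO2, but who obtains it is not stated, and an FiO2 value alone need not identify the arm.
- **A quantified bias.** A reader might try to put a number on the bias in the primary outcome. Suppose PaO2/FiO2 is normal with 40% below 300, and recorded FiO2 is wrong by 5%, so that the effective cut is 315 or 285. The 40% rate becomes 49.9% or 30.7% with SD 60, 47.4% or 33.0% with SD 80, and 44.9% or 35.3% with SD 120: a shift of roughly 5 to 10 points, depending on an SD that the article does not give. Nor does anything tie a 5% error to the coordinator's knowledge of the arm. Since only oxygen flow is titrated in the control arm, an error in deriving FiO2 there could arise with a perfectly blinded recorder.
- **All later outcomes unblinded.** A reader might conclude that blinding survives only for complication classification, because antibiotics, chest X-rays, noninvasive ventilation (NIV) and ICU admission are decided by unmasked clinicians. Blinding of clinicians was never claimed, and gas exchange after discontinuation, length of stay and mortality can also be recorded blind.

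**Conclusion.** The point holds as an internal contradiction. The article claims blinded assessment and blinded recording without exception, yet assigns to that record items that disclose the allocation or are taken while the device is worn. The stated blinding cannot be relied on for one-hour hypoxemia, one-hour gas exchange, discomfort, side effects or complications noted before removal. It remains attainable for outcomes assessed after removal.

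Its size is exposure to bias, not a measured bias. The conclusion assumes only that the two devices can be told apart by sight and that the recorder named in the article is the one who records the listed items. It does not imply that the primary result will be biased by any particular amount, and the sample size is unaffected. It should be corrected because it changes what readers may conclude about the primary outcome, but it does not invalidate the trial.

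**What to change.** 1. **Split the CRF at device removal.** The treating team, already unblinded, records all items up to that moment: side effects, discomfort, device settings and FiO2. PaO2 is taken from the analyzer output.
2. **Give the blinded coordinator a separate form** for outcomes after removal, with no device or side-effect fields, to be opened only once the device is off.
3. **Restrict the claim.** Call blinded only the outcomes assessed after removal: classification of day 1 to 7 complications, gas exchange after discontinuation, length of stay and mortality. Call one-hour hypoxemia, one-hour gas exchange, discomfort and side effects open-label. Add that NIV, intubation and ICU admission follow decisions of clinicians who are not masked.

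The cost is a weaker blinding label and a CRF reissue at three centers while the trial is enrolling, with no gain for patients already recorded. No staff, procedure or sample size is added. The change protects the later complication assessment and corrects the description of the primary outcome. It does not blind discomfort, which patients rate themselves, and it does not remove any error in deriving FiO2 in the control arm, which is a separate issue.
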